#### Patients

Patients aged 18 years and older, presenting with one of the unexplained complaints mentioned above, who have not consulted their GPs for this complaint in the previous 6 months and who are able to speak, read and write Dutch are eligible to be included in the study. GPs decide to ask patients to participate in the study after history taking and physical examination, so the decision to label the complaints of a patient as unexplained is made entirely by the GPs. Excluded are patients with unexplained complaints for whom the GPs feel that watchful waiting would be unacceptable to them. Patients are asked to participate by their GPs. The GPs are asked to enrol each consecutive eligible patient.

### Blinding

#### Researchers

The researchers are not blinded for the trial group allocation of the participating GPs. They are not involved in the GPs' decision to label patients as having unexplained complaints, nor in the test ordering procedure or the reporting of the results of the laboratory tests.

#### GPs

The GPs are not blinded for the trial group they are randomised to, but they are for the content and format of the quality improvement strategy that aims to support GPs in postponing test ordering. In addition, only those test results from the set of tests we decided to include in the study (see the section entitled 'Diagnostic intervention at patient level' below) they ordered themselves are fed back to them, so they are partially blinded to the test results. Since the effects of test results on the treatment given to patients and on their clinical course are outcome measures of our study, we do not aim at complete blinding to the test results.

#### Patients

Patients in group 1 are fully informed about the blood testing options, whereas patients from groups 2 and 3 are kept naive about the possibility of getting blood tests ordered. All patients are blinded for the possibility that their GP is participating in a quality improvement strategy. In our opinion, full blinding is not possible because there is no placebo for blood testing that is feasible and ethically acceptable.

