#### Informed consent procedure

GPs hand out written information and an informed consent form to eligible patients. Patients are given the opportunity to read the information and think about participation before signing the consent form. Patients in group 1 are fully informed about the trial. Patients in groups 2 and 3 are kept naive about the possibility of immediate blood test ordering. This is because it is impossible to blind patients for the test group they are in (immediate or postponed blood test ordering). Bias could be caused by selective dropout of patients and by a Hawthorne effect, as patients can be expected to prefer immediate test ordering over a watchful waiting policy. Patients in groups 2 and 3 are told that the study investigates the way their GPs manage patients with unexplained complaints.

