#### Content of quality improvement strategy

For each GP in group 3, the strategy consists of two small-group meetings and one outreach visit by the researchers to their practice. Table 2 provides more details on the content of the strategy. The first group meeting is led by a GP experienced in medical diagnostic decision-making and a behavioural scientist experienced in teaching communication skills, while the second meeting is tutored only by the behavioural scientist. The outreach practice visit is made by one of the researchers. We have also developed patient education leaflets and diaries, to be handed out by the GPs, and a video message about watchful waiting, to be shown in the waiting room. All materials have been developed by the research team.

**Table 2 T2:** Elements of the quality improvement strategy

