**Elements of strategy**	
Contents of programme	Small group meeting 1 Part 1: Interactive explanation of diagnostic value of diagnostic testing for unexplained complaints and effect of watchful waiting policy on diagnostic value. Part 2: Discussion of difficulties experienced in practice when dealing with patients presenting with unexplained complaints. Goal setting to change behaviour in GPs' own practice. Small group meeting 2 Part 1: Discussion about experiences with behaviour change. Searching for solutions to barriers that have arisen. Part 2: Practicing difficult situations by means of video vignettes. Setting new goals to change own behaviour. Practice visit Discussing individuals' barriers to change and providing suggestions to overcome these, based on stage of change. In between meetings, GPs get the opportunity to work on their goals to change their behaviour.

Materials	– Course book. – Leaflets for patients with information about unexplained complaints. – Diaries about complaints and food intake to hand out to patients to fill in and later discuss together. – Video message for the waiting room, explaining the use of watchful waiting.

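### Equal patient naivety in groups 2 and 3 is not assured, because group 3 alone shows a waiting-room video on watchful waiting, and selective entry into that comparison should be checked by group

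*Protocol article*

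**What the plan says.** All references are to the protocol article.

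- **Informed consent procedure:** "Patients in groups 2 and 3 are kept naive about the possibility of immediate blood test ordering". The reason follows: "Bias could be caused by selective dropout of patients and by a Hawthorne effect, as patients can be expected to prefer immediate test ordering".
- **Blinding, Patients:** the claim is repeated in a wider form, no longer limited to immediate testing: "patients from groups 2 and 3 are kept naive about the possibility of getting blood tests ordered". The same paragraph adds: "All patients are blinded for the possibility that their GP is participating in a quality improvement strategy".
- **Content of quality improvement strategy:** the meetings and practice visit are for group 3 GPs ("For each GP in group 3, the strategy consists of two small-group meetings and one outreach visit by the researchers to their practice"). The materials include "a video message about watchful waiting, to be shown in the waiting room", listed in Table 2 as "Video message for the waiting room, explaining the use of watchful waiting".
- **Control group:** group 2 is offered no strategy, to keep the contrast as large as possible.
- **Clustered randomised clinical trial; Procedure; Participants, Patients:** practices are the randomised units. The GP invites and enrols a patient after history taking and examination.
- **Non-inclusion analysis:** included patients are to be compared with eligible patients who were not included. No comparison by group is stated.

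**The concern.** The naivety statements treat groups 2 and 3 alike, but one component of the group 3 strategy speaks directly to patients in the place where they wait to see the GP. Nothing in the article reconciles the two.

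Group 2 versus group 3 is the quality improvement comparison, and its primary outcome is the quantity of tests ordered. In a trial that randomises practices and enrols patients afterwards, anything that differs by arm before consent can change who enters. If patients who want a test enrol at different rates in the two groups, the proportion tested differs even when the strategy has no effect. The intention-to-postpone analysis cannot repair this, because the selection would occur before enrolment. A non-inclusion analysis pooled over groups could miss it.

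**Working it through.** **Passages side by side**

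| Step | Group 2 | Group 3 | Section |
|---|---|---|---|
| Practice allocated | yes | yes | Clustered randomised clinical trial |
| Watchful-waiting video in waiting room | no | yes | Content of quality improvement strategy; Table 2; Control group |
| History, examination, eligibility, consent | after allocation | after allocation | Procedure; Participants, Patients |
| Stated naivety | naive | naive | Informed consent procedure; Blinding, Patients |

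The second row differs between the groups and the fourth does not. That the video comes before consent is an inference from its location. It is a sound one, but the article does not state it. Nor does the article say whether the video mentions blood tests or the trial, when showing began, or whether every group 3 practice used it.

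**How much room there is for selection**

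The only relevant figure in the article is the patient refusal rate of about 50% under Power calculation, used there to set the number of GPs. Reproducing that chain:

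- Patients: 100 / 0.02 = 5000.
- Patients per GP per year: 500 × 12 × 0.03 = 180, taking the midpoint of 1–5%.
- GPs: 5000 / 180 = 27.8 (stated 27).
- GPs after refusal: 27.8 / 0.5 = 55.6 (stated 54, which is 27 / 0.5).

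The stated figures agree to within 3%. With half of eligible patients expected to refuse, there is room for the enrolled half to differ between groups.

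**Illustration with no true strategy effect**

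The inputs are assumed, except that consent is 50% for everyone in group 2 and for patients without a preference in group 3. Let p be the share of eligible patients who prefer testing (0.2 or 0.4) and c their consent rate in group 3. Early testing is assumed to be 60% in those patients and 20% in the others.

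- Share of test-preferring patients among those enrolled: w = p·c / (p·c + (1 − p)·0.5)
- Proportion tested: 0.60·w + 0.20·(1 − w) = 0.20 + 0.40·w

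In group 2, w = p, so the proportion tested is 28.0% (p = 0.2) or 36.0% (p = 0.4).

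| c in group 3 | w, p = 0.2 | tested | shift (points) | w, p = 0.4 | tested | shift (points) |
|---|---|---|---|---|---|---|
| 0.6 | 0.12/0.52 = 0.231 | 29.2% | +1.2 | 0.24/0.54 = 0.444 | 37.8% | +1.8 |
| 0.5 | 0.10/0.50 = 0.200 | 28.0% | 0 | 0.20/0.50 = 0.400 | 36.0% | 0 |
| 0.4 | 0.08/0.48 = 0.167 | 26.7% | −1.3 | 0.16/0.46 = 0.348 | 33.9% | −2.1 |
| 0.3 | 0.06/0.46 = 0.130 | 25.2% | −2.8 | 0.12/0.42 = 0.286 | 31.4% | −4.6 |
| 0.2 | 0.04/0.44 = 0.091 | 23.6% | −4.4 | 0.08/0.38 = 0.211 | 28.4% | −7.6 |

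A negative shift flatters the strategy and a positive one works against it. The table shows how the mechanism works and is not an estimate, since the article gives no data on c, p or the testing rates.

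**The case against.** A reader might infer that the protection is absent in group 3, because waiting in this trial means postponing blood tests. The documents do not support that. The video is described only as explaining watchful waiting, and the consent section limits the naivety to immediate testing. A message in favour of waiting need not reveal that other patients are tested at once. Nor would seeing the video necessarily tell a patient that the GP is in an improvement programme. This part of the objection stands in full.

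A reader might also infer that any bias must favour the strategy, because patients who want tests would decline in group 3. That is not supported either. Under Watchful waiting for 4 weeks, testing is allowed when a patient insists, so enrolling need not cost such a patient the test. The video could equally make these patients more willing to take part. The article names selective dropout and a Hawthorne effect as its worries. Selective consent is a reasonable extension of the same patient preference, but the extension is ours.

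Two further points are fair. First, addressing patients is a deliberate part of the strategy: the section Improvement of test ordering says patients play a role in the decision to test. If the video lowers demand among enrolled patients, that is a strategy effect. Second, selection at entry is not peculiar to the video. GPs know their group, decide whom to invite, and may exclude patients for whom waiting seems unacceptable. Naivety is imperfect in group 2 as well, since patients there may also insist on a test.

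Finally, a breakdown of the non-inclusion analysis is detail that an article may leave to a fuller plan. The unreconciled naivety statements are not of that kind: they are made in this text and sit beside a group 3 component that puts them in doubt.

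**Conclusion.** The point holds in a limited form. The article claims the same naivety for groups 2 and 3 while giving group 3 alone a patient-facing message that is likely to be seen before consent. Equal naivety is therefore not assured, and selective entry could affect the group 2 versus group 3 comparison of tests ordered. Its size and direction are unknown. The range of −7.6 to +1.8 points rests on assumed preference shares, testing rates and consent differences, and should not be quoted as an expected bias.

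The conclusion depends on one inference, that patients see a waiting-room video before the consultation in which they consent. It does not depend on the video mentioning blood tests. If it did mention them, the conflict with the blinding statement would be direct; without the content, that cannot be said.

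**What to change.** 1. In Informed consent procedure and in Blinding, Patients, state that group 3 patients may meet the watchful-waiting message before consent and that equal naivety in groups 2 and 3 is not assured. Use the same scope in both places, as one now speaks of immediate testing and the other of testing at all.
2. Carry out the non-inclusion analysis separately by group. Set group 2 against group 3 on the numbers eligible, refused and enrolled, and on the available characteristics of enrolled patients. Interpret the comparison of tests ordered in that light.
3. Bound that comparison for any difference in refusal only as far as the recorded data allow. Data collection has ended, and the article does not say that testing was recorded for patients who were not enrolled, so a full reanalysis including them cannot be promised.

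The cost is a less favourable blinding claim and a little extra analysis within work already planned. The design and the strategy stay as they are.

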#### Laboratories

Laboratories are blinded for all patient characteristics except sex and age.

### Diagnostic intervention at patient level

#### Selection of blood tests

Members of an expert panel including GPs and hospital specialists (n = 20) have been individually asked to propose tests which they regarded as useful diagnostic tools in general practice for each of the 5 complaints. All tests mentioned at least twice were included in a complaint-specific set of tests (table 1). If not already included in the set, the four tests recommended in the NHG guideline (glucose, ESR, TSH and Hb) were added. In addition, iron parameters (transferrin saturation (TS) and ferritin), anti-endomysium and carbohydrate deficient transferrin (CDT) were added as indicators of haemochromatosis, celiac disease and alcohol abuse respectively. These three diseases can lead to unexplained complaints, are frequently missed by GPs according to the literature and should be demonstrable with the above blood tests. The diagnostic accuracy of these tests in patients presenting with unexplained complaints in general practice has, however, not yet been established.[12,17-20]

**Table 1 T1:** Sets of laboratory tests per complaint

	**Fatigue**	**Abdominal complaints**	**Musculo- skeletal complaints**	**Weight changes**	**Itch**
Alkaline Phosphatase (AF)	x	x		x	
Alanine aminotransferase (ALAT)	x	x		x	x
Amylase		x		x	
Anti-endomysium		x		x	
Aspartate aminotransferase (ASAT)	x	x		x	
Bilirubin					x
Erythrocyte sedimentation rate (ESR)	x	x	x	x	x
Carbohydrate-deficient transferrin (CDT)	x	x		x	x
Creatinin kinase (CK)			x		
Creatinin	x	x	x	x	x
C-reactive protein (CRP)		x			
Differentiated leukocyte count	x	x		x	x
Eosinophils					x
Ferritin	x	x	x	x	
Gamma glutamyl transferase (GGT)	x	x		x	x
Glucose	x	x	x	x	x
Haemoglobin (Hb)	x	x	x	x	x
Potassium (K)	x		x		
Latex fixation test			x		
Lactate dehydrogenase (LDH)	x			x	
Leukocyte count	x	x		x	x
Monosticon	x				
Total IgE		x			x
Thyroid stimulating hormone (TSH)	x	x	x	x	x
Transferrin saturation (TS)	x	x	x	x	
Urea					x
Uric acid			x		
**Total number of tests**	**17**	**18**	**11**	**17**	**14**

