#### Immediate blood test ordering

GPs from group 1 are instructed to order blood tests immediately when including a patient in the study. The GPs are free to decide on the number and type of blood tests. The patient takes the blood test ordering form to the regional laboratory participating in the study. At the laboratory, the tests ordered by the GP are supplemented by the complaint-specific tests from the sets described in table 1. Only results of tests ordered by the GPs themselves are fed back. If a GP does not intend to order any tests (but is obliged to do so by the study protocol), the results of the four tests recommended by the NHG guideline are fed back, because patients expect results after a blood sample has been taken.

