#### Reference standard

The nature of unexplained complaints implies that no proper gold standard exists. Hence, we opted for a delayed type cross-sectional study design.[21,22] In this type of design, the diagnosis after the 12-month follow-up period is used as a reference standard. This diagnosis is established separately by two researchers, making use of information from the GPs' patient records. Differences are discussed and consensus is sought. If consensus cannot be reached, the case is presented to an expert panel that takes the final decision. No restrictions are imposed on GPs as to patient management during follow-up.

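### For four laboratory-added markers whose results are withheld, PPV against the GP record is understated by an unknown amount and should not be read as diagnostic accuracy

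*Protocol article*

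**What the plan says.** Four statements in the Protocol article combine.

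- *Selection of blood tests.* TS and ferritin, anti-endomysium and CDT are added as indicators of haemochromatosis, coeliac disease and alcohol abuse. One reason given is that these diseases "are frequently missed by GPs according to the literature and should be demonstrable with the above blood tests". The section adds: "The diagnostic accuracy of these tests in patients presenting with unexplained complaints in general practice has, however, not yet been established". So these markers are included in order to be evaluated.
- *Immediate blood test ordering.* At the laboratory, "the tests ordered by the GP are supplemented by the complaint-specific tests from the sets described in table 1". Then: "Only results of tests ordered by the GPs themselves are fed back". A GP who would have ordered nothing receives only the four guideline tests (glucose, ESR, TSH, Hb), none of which is an added marker. The Blinding section states the same feedback rule for GPs in general.
- *Reference standard.* Here "the diagnosis after the 12-month follow-up period is used as a reference standard". On its source: "This diagnosis is established separately by two researchers, making use of information from the GPs' patient records". A panel enters only on disagreement: "If consensus cannot be reached, the case is presented to an expert panel that takes the final decision".
- *Primary outcome measures of the diagnostic intervention.* Accuracy for serious pathology, per test and in combinations, is the first primary outcome.

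**The concern.** The reference diagnosis comes from a source that the article itself expects to miss these three diseases, and the result most likely to prompt the diagnosis is kept from the person who writes the record. If a patient has the disease, tests positive on a marker the GP did not order, and is still undiagnosed at 12 months, the 2x2 table counts that positive as false.

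The error is one-sided for PPV. It also bears on the trial's central argument, which is that testing patients at low prior probability yields too many false positives. An apparently poor PPV for the newer markers would fit that argument, yet part of it could come from the feedback rule and the choice of reference source.

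**Working it through.** **Inputs.** The article gives no prevalence, sensitivity, specificity or miss rate for the three diseases; its statement that GPs often miss them carries no number. Its only related figure is 2% serious pathology from all causes, used for sample size (100/0.02 = 5000). That arithmetic reproduces and is not in question. All values below are assumptions.

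**Model.** Let p be prevalence, Se and Sp the true sensitivity and specificity, r+ the share of diseased test-positives recorded by 12 months, and r- the same share for diseased test-negatives. Assume the record contains no wrong positive diagnoses. As proportions of those tested:

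- true cells: TP = p·Se; FN = p·(1-Se); FP = (1-p)·(1-Sp); TN = (1-p)·Sp
- observed cells: TP' = r+·TP; FP' = FP + (1-r+)·TP; FN' = r-·FN; TN' = TN + (1-r-)·FN

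**PPV.** The number of positives does not change (TP' + FP' = TP + FP), so

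apparent PPV = r+·TP/(TP + FP) = r+ × true PPV.

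This identity holds whatever p, Se and Sp are.

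**Illustration.** p = 1%, Se = 90%, Sp = 99%. TP = 0.01 × 0.90 = 0.0090; FP = 0.99 × 0.01 = 0.0099; true PPV = 0.0090/0.0189 = 47.6%. With r+ = r-:

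| Share recorded | Apparent PPV | Apparent specificity | Apparent sensitivity |
|---|---|---|---|
| 100% | 47.6% | 99.0% | 90% |
| 50% | 0.0045/0.0189 = 23.8% | 0.9806/0.9950 = 98.6% | 90% |
| 20% | 0.0018/0.0189 = 9.5% | 0.9809/0.9980 = 98.3% | 90% |
| 10% | 0.0009/0.0189 = 4.8% | 0.9810/0.9990 = 98.2% | 90% |

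**Other assumed values.**

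- p = 0.5%: true PPV 31.1%, falling to 15.6% (half recorded) or 6.2% (a fifth).
- p = 2%: 64.7%, falling to 32.4% or 12.9%.
- p = 1% with Sp = 98%: 31.2%, falling to 15.6% or 6.2%.
- Specificity moves by more than one point only towards the edge of this range: with p = 2%, Se = 90%, Sp = 98% and a fifth recorded, it goes from 98.0% to 96.6%.

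**Sensitivity.** Apparent sensitivity = r+·Se/[r+·Se + r-·(1-Se)]. With r+ = r- it equals Se. If diseased test-negatives are recorded less often, it is too high: r+ = 0.5 and r- = 0.2 give 0.45/(0.45 + 0.02) = 95.7% against a true 90%.

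**The case against.** The case for leaving the plan alone has several parts.

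- *The diagnosis may still surface.* GPs choose their own tests and may order these markers. Patients who return after 4 weeks are tested in every arm. On follow-up the article says: "No restrictions are imposed on GPs as to patient management during follow-up". This stands as a limit: only diseased patients still unrecorded at 12 months are affected. A reader might infer that all true positives become false positives, or that sensitivity rests only on cases found without the test. The text supports neither, because GP-ordered results are fed back.
- *Withholding has a purpose.* It keeps added results from shaping the diagnosis they are judged against, and the article openly says that no proper gold standard exists. Both are fair. But for diseases that the record often misses, withholding exchanges one bias for another, and the general caveat does not address these markers. The protection is also partial, since GP-ordered results can still influence the record.
- *Two readers and a panel.* These resolve disagreement. Two readers can agree on a record that lacks the diagnosis, and then the panel never sees the case.
- *The researchers hold the result forms.* The Reference standard section does not name those forms as a source. If they were used, the index test would help define its own reference.
- *The target is serious pathology, not each disease.* Correct. Prevalence in the model must be read as cases that need treatment, and the article does not say how many undiagnosed cases would qualify. The PPV identity is unaffected.
- *This belongs in an analysis plan that is not shown.* Handling might be described there. The bias, however, follows from rules that the article states, not from detail it omits.
- *Simple bounds would say little.* True. If no withheld positive were worked up, bounds in the example would run from 9.5% to 100%. A sensitivity analysis over stated recording shares is more useful.

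**Conclusion.** The point holds for laboratory-added anti-endomysium, CDT, TS and ferritin results that the GP did not order. For these, the 12-month GP-record diagnosis is an insensitive reference standard by the article's own account, and apparent PPV is true PPV times the share of diseased test-positives recorded.

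Direction and form follow from the text, given that recorded diagnoses are correct. Size does not: the fall from 48% to 24% or 9.5% is set by assumed inputs, and one scenario stands in for three diseases and four markers. A reader might infer that specificity is badly distorted as well. In the main illustration it drops by less than one percentage point, so PPV is the measure at risk. Sensitivity is unchanged, or overstated if test-negatives are recorded less often.

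Reach is limited. Four of the 27 tests in Table 1 are involved, and not for every complaint: anti-endomysium is run for abdominal complaints and weight changes only, CDT is not run for musculoskeletal complaints, and the iron tests are not run for itch.

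**What to change.** For these four markers:

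1. Report results separately for GP-ordered (fed-back) and laboratory-added (withheld) tests. The ordering and result forms needed for this are already collected (Measurements, Patients). State that the fed-back subset is selected by GP suspicion and open to verification driven by the known result, so it is not an unbiased benchmark.
2. For withheld results, label PPV as agreement with GP-recorded diagnosis and a likely lower limit. Give the positivity rate and the number of positives without a recorded work-up.
3. Add a sensitivity analysis over assumed r+ and r-, varied separately. Use TP = TP'/r+ and FN = FN'/r-, taking the added cases out of FP' and TN'. Corrected PPV is then apparent PPV/r+: an observed 9.5% would correspond to 19% at r+ = 0.5 and 48% at r+ = 0.2, and r+ cannot be below 0.095.
4. Do not conclude from withheld results alone that these tests mostly give false positives.

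The cost is some extra analysis and weaker claims about four of the 27 tests. Testing and the withholding rule stay as they are. The article reports that data collection has ended and that cleaning and analysis are in progress, and this change needs no new data.
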